### 8.4.1 *Stopping criteria for dose escalation*

The Principal Investigator and the iSRC (Section 8.4.3) will follow the recommendations and grading system of Common Terminology Criteria for Adverse Events (CTCAE) v5.0, see Section 11.7.1.7 but also take into account the recommendations published by Sibille *et al.* 2010, which is an adaptation to FIH studies of the grading systems previously proposed by National Cancer Institute (NCI), World Health Organization (WHO), National Institute of Health (NIH) and the US Food and Drug Administration (FDA). The grade, the frequency of AEs and the blindness will be considered.

A rolling review of emerging safety data will be performed throughout the study taking into account any AEs and their relation to pharmacodynamic (PD) effects, the number of subjects in whom they occur, concurrency of more than one event within the same subject and any trends. Changes from baseline measurements will also be considered and not just absolute cut-off based on upper- or lower limits of normal that might apply for healthy volunteers.

Trends or safety signals described above, which are not necessarily covered by the stopping criteria in Table 8.4-1 may warrant the scheduling of ad hoc iSRC meetings after which the iSRC will make recommendations to Sponsor on e.g. whether to terminate the study or to stop dosing in individual subjects or a certain cohort.

Stopping criteria related to exposure (area under the curve [AUC] and maximum plasma concentration [ $C_{max}$ ] of CXCL12) are considered as not applicable for the study since the systemic exposure of CXCL12 is predicted to be very low or undetectable.

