| If no subject has an SAE considered at least possibly related to the IMP administration, i.e. a serious adverse drug reaction (SADR)                                                                | Escalate to the next higher dose level.                                                                                                                                                                                                                                                                                                                                                                                                                                                                                                                                                                                                                                                                                                                                                                                                          |
| If 1 subject has an SAE assessed as at least possibly related to IMP administration                                                                                                                 | 
 
1) Stop of further dosing at this dose level
 
2) If the SAE is clearly associated with a single, or multiple wound(s): unblinding of these wounds. Only voting members of the iSRC will be unblinded.

If the etiology of the SAE is not obviously associated with a single, or multiple, wound(s), no unblinding will be performed. The SAE will be regarded as related to ILP100-DP.
 
3) Evaluation by iSRC. The iSRC makes recommendation to Sponsor.

Subject meets stop criterion: stop further dosing at this dose level for all subjects. Sponsor decides if the study will be terminated or if dosing will commence at a lower dose level or at an intermediate dose level.
 
                                                                            |

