| If 2 subjects on active treatment have severe, non-serious AEs assessed at least possibly related to the IMP administration (independent of within or not within the same System organ class [SOC]) | 
 
1. Stop dosing of subjects with severe, non-serious potential ADRs.
 
2. If the AEs are clearly associated with a single, or multiple wound(s): unblinding of these wounds. Only voting members of the iSRC will be unblinded.

If the etiology of the AEs is not obviously associated with a single, or multiple, wound(s), no unblinding will be performed. The AEs will be regarded as related to ILP100-DP.
 
3. Evaluation by iSRC. The iSRC makes recommendation to Sponsor.
 
4. Sponsor decides how to proceed:

Both subjects meet stop criterion: stop further dosing at this dose level for all subjects. Sponsor decides if the study will be terminated or if dosing should commence at a lower dose level or at an intermediate dose level.
 
 |
| If 2 subjects in different cohorts have SAEs assessed as at least possibly related to IMP administration                                                                                            | 
 
1. Stop dosing of subjects with potential SADR.
 
2. If the SAEs are clearly associated with a single, or multiple wound(s): unblinding of these wounds. Only voting members of the iSRC will be unblinded.

If the etiology of the SAEs is not obviously associated with a single, or multiple, wound(s), no unblinding will be performed. The SAEs will be regarded as related to ILP100-DP.
 
3. Evaluation by iSRC. The iSRC makes recommendation to Sponsor.

Both subjects meet stop criterion: Termination of study.
 
                                                                                                                                                                                                                                      |

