#### 8.4.3 *Internal safety review committee*

Before initiating a new cohort, all subjects in the previous cohort must have been treated and 3 days (SAD) and 21 days (MAD) safety and tolerability data for all treated subjects must have been evaluated by the iSRC. Based on emerging safety and tolerability data, the amount of required safety data to be reviewed after a completed cohort might be adjusted. Details regarding timing of iSRC review and the data to be reviewed and the documentation procedure will be provided in a separate iSRC charter.

The voting members of the iSRC will consist of the Principal Investigator, the Medical Monitor (i.e. the Sponsor's medically responsible person) or delegate and an independent, external clinical expert. The clinical research manager (CRM), and additional Sponsor representatives will be invited as appropriate. Further internal or external experts may be consulted by the iSRC as necessary.

An adaptive dosing strategy will be applied to allow for a flexible and safe dose escalation. The planned dose escalation is outlined in Section 8.3.1. The actual doses given in each cohort will be guided by the iSRC recommendations based on available safety and tolerability data. Every dose step is thus adjustable and the recommendation to the Sponsor may be to continue with a higher or lower dose than the intended dose, repeat the same dose level, continue with an intermediate dose level or to stop dosing.

The decision of the iSRC on the recommendation of the next dose level will be taken in consensus between the iSRC members and documented as appropriate. In case there is disagreement between the 3 voting members, the most conservative approach will be taken. It is not acceptable to repeat a dose level where any of the dose escalation stopping rules have been met.

The treatment code for individual wounds may be broken by the iSRC during the assessment process (partial un-blinding) in accordance with stopping criteria described in Table 8.4-1. The medical staff and the subjects will still be blinded for the treatments (active drug, placebo or saline) to be administered in the subsequent dose groups/cohorts in order to minimize bias. If unblinding was considered necessary, the iSRC meeting may consist of a closed part and an open part.

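### Table 8.4-1: after two subjects have severe, related, non-serious AEs, the other subjects at that dose level are not held while the iSRC evaluates

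*Protocol*

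**What the plan says.** Table 8.4-1 has four rows. Row 1 allows escalation when there is no related SAE. Rows 2 to 4 set out what to do when a safety event occurs.

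- **Row 2** (one subject with a related SAE) opens with "Stop of further dosing at this dose level". Unblinding of implicated wounds and iSRC evaluation follow.
- **Row 3** (two subjects with severe, non-serious, related AEs) opens with "Stop dosing of subjects with severe, non-serious potential ADRs". Unblinding of implicated wounds is step 2 and iSRC evaluation is step 3. Step 4 is the sponsor's decision, and only there does the row say "Both subjects meet stop criterion: stop further dosing at this dose level for all subjects".

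Outside the table, Section 8.4.1 states that "A rolling review of emerging safety data will be performed throughout the study". It adds that trends or signals "may warrant the scheduling of ad hoc iSRC meetings after which the iSRC will make recommendations to Sponsor", and stopping a cohort is among the recommendations it gives as examples. Section 8.4.3 contains the gate between cohorts ("Before initiating a new cohort, all subjects in the previous cohort must have been treated") and a ban on repeats ("It is not acceptable to repeat a dose level where any of the dose escalation stopping rules have been met"). On when the committee meets, it says "Details regarding timing of iSRC review and the data to be reviewed and the documentation procedure will be provided in a separate iSRC charter".

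**The concern.** Row 3 recognises that two severe related reactions may mean that nobody else should be dosed at that level. Yet between the trigger and the decision it names only the two people who have already reacted. The others at the level are healthy volunteers with no medical benefit from the trial. They are due the same active dose, and the row neither stops nor clears them. A hold that proves unnecessary can be lifted; a dose already applied cannot be taken back. This is a first-in-human study of a living genetically modified product, and Section 6.3 itself says that adverse reactions are hard to predict.

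**Working it through.** The protocol gives no figure to reproduce here. The check compares the order of actions, looks for a hold elsewhere in the text, and counts who is left without one.

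**1. Order of actions (Table 8.4-1)**

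| Step | Row 2: one related SAE | Row 3: two severe, non-serious, related AEs |
|---|---|---|
| 1 | Dose level stopped | Affected subjects stopped |
| 2 | Implicated wounds unblinded, if any | Same |
| 3 | iSRC evaluates; if the criterion is met, the stop is for all subjects and the sponsor decides what follows | iSRC evaluates and recommends |
| 4 | – | Sponsor decides; level-wide stop if both subjects meet the criterion |

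Both rows can end in a level-wide stop. Only row 2 protects the rest of the level while the question is open. Row 4 (two related SAEs in different cohorts) is also worded at subject level, but each of those SAEs would already have triggered row 2 for its own level. Row 3 is therefore the only row with no interim hold.

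**2. Is the gap filled elsewhere?**

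- Rolling review and ad hoc meetings (8.4.1): discretionary, and they lead to a recommendation. There is no automatic hold.
- Gate before a new cohort (8.4.3): concerns the next cohort, not subjects still to be dosed in the current one.
- Repeat ban (8.4.3): limits the choice of the next dose level, not dosing already under way.
- SAE definition (11.7.1.2): events requiring hospitalization, and doubtful cases, count as SAEs and fall under row 2. Severe events judged non-serious remain, and these are what row 3 covers.

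**3. What step 1 achieves in the SAD part.** Each subject is dosed once (8.1.1). A subject who has reacted after dosing has no dose left, so stopping that subject withholds nothing. The only doses that could still be withheld belong to subjects not yet treated, whom step 1 does not mention.

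**4. Subjects without a hold, both affected subjects in the same cohort**

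SAD: cohort of 4, at most 2 dosed per day (8.1.1), so at least 4 / 2 = 2 dosing days. If both reactions are known after k subjects have been dosed, 4 − k remain:

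- k = 2: 4 − 2 = 2
- k = 3: 4 − 3 = 1
- k = 4: 4 − 4 = 0

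Range 0 to 2; upper bound 2 / 4 = 50%.

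MAD: cohort of 8, at most 4 dosed per day (8.1.2), so at least 8 / 4 = 2 start days.

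- Both affected subjects among the first four, second four not started: (4 − 2) + 4 = 6
- All eight started, with doses left: 8 − 2 = 6
- All eight past the last dose: 0

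Range 0 to 6; upper bound 6 / 8 = 75%.

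**5. Illustration of doses in the interval (MAD).** The protocol gives no length for the iSRC review, so 1 to 7 days is an assumption. Nominal dosing days are 1, 2, 3, 5, 8, 10, 12, 15, 17 and 19 (8.1.2, Table 8.1-2). For an unaffected subject on that schedule, with the interval starting on any dosing day before the last, the further doses falling inside it are:

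- 1-day review: 0 to 1
- 3-day review: 1 to 2
- 7-day review: 1 to 4

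These counts show that the interval can contain doses. They do not predict how many would be given.

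**The case against.** The strongest reply is that row 3 is a deliberate graded response. An SAE is graver than a severe non-serious event, so the level stops at once for the first and only after evaluation for the second. Every subject carries control wounds as well as active ones, so a severe local reaction may belong to placebo or saline, and attribution should come before a level-wide stop. The principal investigator and the medical monitor vote on the iSRC and would know of the events, an ad hoc meeting can recommend stopping a cohort, and the unseen charter may provide for review before the next dose.

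Part of this stands. A graded response may be intended, the class of events is narrow, the discretionary route is real, and if review came before the next dose nobody would be exposed. But grading is already expressed by the higher trigger, two subjects instead of one. It does not explain continued dosing once that trigger is met, and the protocol gives no such rationale. Attribution does not explain it either. Row 2 also unblinds wounds, yet stops first. In row 3, events not clearly tied to particular wounds are already treated as related to ILP100-DP, and everyone in the cohort receives the active product at that level. Nor does grading explain a SAD step that withholds no dose. Section 8.4.3 leaves to the charter the timing of review, the data and the documentation; it does not say that the charter sets an interim hold.

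**Conclusion.** The concern holds. From the row 3 trigger until the sponsor's decision, the protocol has no automatic hold for unaffected subjects at the dose level, whereas row 2 has one from step 1. If both affected subjects are in the same cohort, the number left without a hold is 0 to 2 of 4 in the SAD part (at most 50%) and 0 to 6 of 8 in the MAD part (at most 75%), depending on how many are still due a dose. These figures count subjects not covered. They are not doses given or a measure of risk, and no dose count is claimed because the timing of iSRC review is not in the protocol. The gap does not invalidate the trial. It is a weakness in a safety rule that should be corrected because the correction is so small.

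**What to change.** Reword row 3 step 1 in Table 8.4-1 so that all further dosing at the dose level is held, including subjects not yet dosed, until the iSRC has evaluated, as row 2 does. Leave the trigger (two subjects) and steps 2 to 4 unchanged.

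The edit is one line. Its operational cost is a possible short pause. In the MAD part this may shift or drop doses for unaffected subjects, because Table 8.1-2 allows ±1 day only on Days 12 to 19 and Section 8.2 aims for equal exposure time across subjects. A hold called on Day 1, after punching, would also collide with the requirement to start application 1 hour (±10%) after the last punch (8.1.1, 8.1.2). It would help to add how such subjects and any missed doses are handled.

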#### 8.4.2 *From single to multiple dosing*

The SAD part of the study will be completed prior to the start of the MAD part. Following completion of the SAD part, the iSRC will evaluate all safety and tolerability data from the SAD and, if necessary, suggest adjustments to dose levels or dosing regimens in a written recommendation to the Sponsor. Dose adjustments or adjustments to dose regimens may be recommended based on the SAD data. If no safety or tolerability concerns are identified, the MAD part will commence as decided by the Sponsor. The iSRC recommendation as well as Sponsor's decision, will be documented in a non-substantial amendment.

#### 8.4.3 *Internal safety review committee*

Before initiating a new cohort, all subjects in the previous cohort must have been treated and 3 days (SAD) and 21 days (MAD) safety and tolerability data for all treated subjects must have been evaluated by the iSRC. Based on emerging safety and tolerability data, the amount of required safety data to be reviewed after a completed cohort might be adjusted. Details regarding timing of iSRC review and the data to be reviewed and the documentation procedure will be provided in a separate iSRC charter.

The voting members of the iSRC will consist of the Principal Investigator, the Medical Monitor (i.e. the Sponsor's medically responsible person) or delegate and an independent, external clinical expert. The clinical research manager (CRM), and additional Sponsor representatives will be invited as appropriate. Further internal or external experts may be consulted by the iSRC as necessary.

An adaptive dosing strategy will be applied to allow for a flexible and safe dose escalation. The planned dose escalation is outlined in Section 8.3.1. The actual doses given in each cohort will be guided by the iSRC recommendations based on available safety and tolerability data. Every dose step is thus adjustable and the recommendation to the Sponsor may be to continue with a higher or lower dose than the intended dose, repeat the same dose level, continue with an intermediate dose level or to stop dosing.

The decision of the iSRC on the recommendation of the next dose level will be taken in consensus between the iSRC members and documented as appropriate. In case there is disagreement between the 3 voting members, the most conservative approach will be taken. It is not acceptable to repeat a dose level where any of the dose escalation stopping rules have been met.

The treatment code for individual wounds may be broken by the iSRC during the assessment process (partial un-blinding) in accordance with stopping criteria described in Table 8.4-1. The medical staff and the subjects will still be blinded for the treatments (active drug, placebo or saline) to be administered in the subsequent dose groups/cohorts in order to minimize bias. If unblinding was considered necessary, the iSRC meeting may consist of a closed part and an open part.

## 9 STUDY POPULATION

Prospective approval of protocol deviations to eligibility criteria, also known as protocol waivers or exemptions, is not permitted.

### 9.1 Recruitment

The subjects will be recruited from [REDACTED] database of healthy volunteers and from advertising in media (including social media).

### 9.2 Screening and enrolment log

Investigators must keep a record of all screened subjects even if they were not subsequently included in the study. This information is necessary to verify that subjects were selected without bias. The reason for screen failure should be stated for all subjects screened but not included. The reason for withdrawal should be stated for all subjects included but not completed.

A screening number will be allocated to each subject in connection to the informed consent process at the Screening visit. The screening number is automatically generated in the electronic case report Form (eCRF). The screening number will allow identification of subjects irrespective of their possible eligibility for the study.

Subjects included and randomized will be assigned a randomization number (1101, 1102 etc. the SAD, cohort 1; 2101, 2102 etc. in the MAD, cohort 1 and so on). The first digit will correspond to the study part, the second digit will correspond to the cohort and the 3rd and 4th digits correspond to the subject number.

If a subject cannot receive the planned dose of IMP within 27 days after screening (*i.e.*, the time interval between signing informed consent until dose administration) the subject should be re-screened before proceeding in the study. For details regarding re-screening, refer to Section 9.7.

### 9.3 Number of subjects

Approximately 90 subjects will be screened (approximately 30 for the SAD and 60 for the MAD) to achieve a total of 36 randomized and dosed subjects. The number may increase if additional dose cohorts need to be investigated and/or if recommended by the iSRC.

SAD: 12 healthy subjects will be randomized and dosed.

MAD: 24 healthy subjects will be randomized and dosed.

To account for potential drop-outs and/or additional cohorts depending on recommendations from the iSRC, additional subjects might be included in the study.

## 9.4 Inclusion criteria

For inclusion in the study, subjects must fulfil the following criteria:

1. Willing and able to provide a written informed consent for participation in the study.
2. Healthy males and females aged  $\geq 25$  and  $\leq 45$  years.
3. Willing and able to comply with study requirements.
4. Non-obese subjects with a body Mass Index (BMI)  $\geq 18.0$  and  $\leq 30.0$  kg/m^2 and weight at least 50 kg and no more than 120 kg at screening.
5. Clinically normal medical history, physical findings, vital signs, ECG and laboratory values at the time of screening, as judged by the Investigator.
6. Women of child bearing potential (WOCBP) must agree to use a highly effective method of contraception with a failure rate of  $< 1\%$  to prevent pregnancy (combined [estrogen and progestogen containing] hormonal contraception associated with inhibition of ovulation [oral, intravaginal, transdermal], progestogen-only hormonal contraception associated with inhibition of ovulation [oral, injectable, implantable], intrauterine device [IUD] or intrauterine hormone-releasing system [IUS]) from at least 4 weeks prior to dose until 3 months after the last dose of IMP and until confirmation of negative 6 weeks skin swab and feces analyses concerning *L. reuteri* R2LC and/or pILP100 findings. Their male partner must agree to use a condom during the same time frame.

Women of non-childbearing potential are defined as pre-menopausal females who are sterilized (tubal ligation or permanent bilateral occlusion of fallopian tubes); or post-menopausal defined as 12 months of amenorrhea (in questionable cases a blood sample with simultaneous detection of follicle stimulating hormone [FSH] 25-140 IE/L and estradiol  $< 183$  pmol/l is confirmatory).

Male subjects must be willing to use condom or be vasectomized to prevent pregnancy and drug exposure of a partner and refrain from donating sperm from the date of dosing until 3 months after the last dose of IMP and until confirmation of negative 6 weeks skin swab and feces analyses concerning *L. reuteri* R2LC and/or pILP100 findings. Their female partner of child-bearing potential must use contraceptive methods with a failure rate of  $< 1\%$  to prevent pregnancy (see above).

7. Subjects must agree to refrain from donating blood/blood components and organs from the first dose of IMP until 3 months after the last dose of IMP and until confirmation of negative 6 weeks skin swab and feces analyses concerning *L. reuteri* R2LC and/or pILP100 findings.

